#### Who will take informed consent? {26a}

Initially, the objectives of the trial will be clarified by the first researcher to the children’s parents and legal guardians, and written informed consent will be obtained from them at the time of enrolment.

#### Additional consent provisions for collection and use of participant data and biological specimens {26b}

In the consent form, the participants will be asked whether they agree upon using their data in case they withdraw from the trial. In addition, their permission will be obtained by the research team to share relevant data with the academic experts selected from the universities partaking in the research or other regulatory authorities. Notably, this trial does not involve the collection of biological specimens for storage.

### Interventions

#### Explanation for the choice of comparators {6b}

The participants in the placebo/control group will receive standard CF treatments, and curcumin will be used as add-on therapy; this is the reason for considering placebo as the control group in our study.

#### Intervention description {11a}

Nano-curcumin (Exir Nano Sina Drug Company, Iran) is prepared as nano micelle in the form of 70 mg of drops in 1 cc, and the placebo with the same color, taste, and odor.

To adjust the drug dose for different ages and considering that the maximum acceptable dose based with the most significant impact and minimum side effects was 80 mg, the required amount will be obtained for each subject based on the ratio of the body surface area of the patients. The curcumin and placebo glasses have been labeled A and B by Exir Nano Sina company, respectively, and made available to the patients through a double-blind design. Curcumin or placebo will be administered orally alone or with sweetened water once daily at bedtime and at a fixed dose for 3 months.

#### Criteria for discontinuing or modifying allocated interventions {11b}

Although no special side effect has been reported until now, with any intervention-related side effects, we will stop the intervention and report it to the Ethics committee of Mashhad University of Medical Sciences (MUMS) for decision making. If the participants request to discontinue treatment or report the deterioration of their condition due to CF, we will stop the intervention.

#### Strategies to improve adherence to interventions {11c}

The strategies adopted to improve the adherence of the patients to the intervention include taking the medicine once a day versus several times, using an oral drop versus a soft gel for easier consumption by children and using the medications and prescribed agents before bedtime so as to minimize interference with other common CF medications. In addition, the individualized training of the patients and their children was performed on the benefits and necessity of the accurate and complete use of the intervention for an optimal impact. The lack of adherence to the drug occurs in cases where less than 70% of the prescribed dose is used, which will be assessed during monthly follow-up sessions.

#### Relevant concomitant care permitted or prohibited during the trial {11d}

Concomitant intervention will be:
Pancreatic enzyme replacement therapy (PERT): All CF patients with pancreatic deficiency need PERT for enzyme replacement. In this regard, we enrolled CF patients with gastrointestinal involvement; all of our patients use Creon as a usual treatment in which doses are adjusted to the level of dietary fat.Antibiotic: Tobramycin inhalation is an antibiotic which is used for pseudomonas infection.Anti-inflammatory: Low-dose azithromycin treatment frequently prescribed chronically that has an anti-inflammatory effect in CF patients 6 years and older. We use it in our patients.Anti-acid: Suggested for patients who fail to respond to maximal dose of PERT and in patients with reflux disease.Inhaled hypertonic saline: Nebulized hypertonic (7%) saline is recommended twice daily to all patients 6 years and older.Inhaled beta2 agonist: Administrated in CF patients with moderate to severe lung disease twice a week.Fat soluble vitamins: For all CF patients with pancreatic deficiency. Notably, the administration of the nano-curcumin drop or nano-curcumin placebo drop will not require any changes in the routine treatment of CF, and the care procedure and medication will continue for both trial arms.

#### Provisions for post-trial care {30}

There is no anticipated harm and compensation for participation in this trial.

#### Outcomes {12}

The primary outcomes of the current trial are the compared changes in the blood vessel inflammation, nasopharyngeal swab, and fecal samples at baseline with 3 months after the intervention: systemic inflammation by assessing IL-6 as an inflammatory agent, IL-10 as an anti-inflammatory agent, and hs-CRP level in the blood samples, pulmonary inflammation with the neutrophil count, bacterial/viral culture on the nasopharyngeal swab, and gastrointestinal inflammation with the calprotectin level in the fecal samples.

The secondary outcomes are changes in clinical assessment of the pulmonary symptoms via spirometry, anthropometric assessment stand on the BMI Z score, and evaluation of the quality of life using the CFQ from the baseline to 3 months of the intervention.

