**Methods:**

This prospective, double blind control trial will be conducted at the Akbar Children’s Hospital in Mashhad, Iran. Children with CF will be enrolled based on the eligibility criteria. Placebo and curcumin with the maximum dose of 80 mg considering the body surface of the patients will be administrated for 3 months. The primary outcome is to evaluate inflammation based on serum interleukin-6, interleukin-10, and hs-CRP, stool calprotectin, and neutrophil count of nasopharyngeal swab. The secondary outcome involved clinical assessment via spirometry, anthropometrics, and quality of life. They will be assessed before and after 3 months.

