#### Sample size {14}

Due to the lack of clinical trials on the inflammatory effect of nano-curcumin in children with cystic fibrosis, we used HSCRP indices as an effect size. Therefore, the mean ± SD of hs-CRP indices in the curcumin and placebo groups were 5.9 ± 2.57 and 3.6 ± 1.58 respectively [27]. G- power analyzer was applied for calculating sample size between two independent populations with a confidence interval of 95% and power of 80%. By considering 10% dropout and using Deff (deign effect) for stratified sample, a total of 30 samples for each group was calculated. In total, 60 eligible patients with CF are needed to be included for the randomization aspect of this research.

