### Data collection and management

#### Plans for assessment and collection of outcomes {18a}

As the primary outcome of the present study, blood vessel inflammation will be assessed in the sample using the ELISA assay (IL-6, IL-10, and hs-CRP), stool inflammation will be determined by measuring the calprotectin level using the ELISA assay, and pulmonary inflammation will be evaluated using the smear and culture (gram-positive, gram-negative, pseudomonas) of the nasopharyngeal soap. All the tests will be performed at the Buali Research Institute by expert personnel. Table 2 shows the performance specifications of the applied methods.

For the quality assurance of the employed laboratory methods, the performance specifications will be verified before using the kits for the analysis of the patient samples. All the tests will be performed in duplicate, and the standard curve will be prepared using the serial dilutions of the standard samples. The obtained results will be calculated from the standard curve after adjustment for the blank.

The secondary outcome of the present study was anthropometric assessment, which will be performed in a standard position using SECA instruments for height and weight. In addition, the WHO growth standard charts will be used for the evaluation of the BMI *z*-score.

In the current trial, we will apply the CFQ-R to assess the effects of nano-curcumin on the quality of life of the children with CF. The CFQ was first developed in France and consists of three appropriate versions for children aged 6–13 years (CFQ-child), as well as the parents of children with CF aged 6–13 years (CFQ-parent) and adolescents and adults with CF aged 14 years (CFQ-teen/adult) [28]. After the psychometric assessment of the original version and slight modifications, the final version of the CFQ-R was developed.

Spirometry will be performed using a spirometer (CHESTGRAPH HI-105), with the patients in a stable, standing position and their neck completely straight. To increase accuracy and reliability, the test will be repeated at least twice. If FVC and FEV1 are more than 150 ml different from the first time, the test will be repeated; the maximum repetition will be eight times.

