#### Statistical methods for primary and secondary outcomes {20a}

Data analysis will be performed in SPSS version 16, and data distribution will be evaluated using the Kolmogorov-Smirnov test. Data are expressed as frequencies for the qualitative variables, mean and standard deviation for the normally distributed continuous variables, and median and interquartile range for the other variables. In addition, intergroup differences will be evaluated using paired t-test for the normally distributed continuous variables and Wilcoxon rank-sum test for the other variables. Intragroup differences will be assessed using independent *t* test for the normally distributed continuous variables and Mann-Whitney *U* test for the other variables. The mean changes in the secondary outcomes will also be adjusted for the baseline data and disease severity using the analysis of covariance (ANCOVA). In all the statistical analyses, the *P* value of ≤ 0.05 will be considered significant.

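### Six co-equal primary outcomes are each judged at P ≤ 0.05 with no success rule or multiplicity control, giving roughly an 18–27% chance of at least one false-positive primary result if any one marker counts

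*Protocol article*

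**What the plan says.** Outcomes {12} of the protocol article groups the primary outcomes by site. For the blood it gives "systemic inflammation by assessing IL-6 as an inflammatory agent, IL-10 as an anti-inflammatory agent, and hs-CRP level in the blood samples". For the airway it gives "pulmonary inflammation with the neutrophil count, bacterial/viral culture on the nasopharyngeal swab". For the gut it gives fecal calprotectin. That is six outcomes if culture counts as one, with no ranking, composite or rule for success.

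The abstract (Methods) lists five and leaves culture out: "serum interleukin-6, interleukin-10, and hs-CRP, stool calprotectin, and neutrophil count of nasopharyngeal swab".

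Statistical methods {20a} says that, for all analyses, a "value of ≤ 0.05 will be considered significant". It does not say whether tests are one- or two-sided. No section splits alpha, sets an order of testing or adjusts for multiple outcomes.

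Sample size {14} rests on a single marker: "we used HSCRP indices as an effect size", at 95% confidence and 80% power. It does not call hs-CRP the main outcome.

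Section {18a} describes the airway assessment as "smear and culture (gram-positive, gram-negative, pseudomonas", and Table 2 lists the same bacterial groups. Neither gives a method for viral culture.

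**The concern.** The sample size calculation treats the trial as one comparison at 5%, while the outcome and analysis sections allow five or six. If a significant result on any one marker can be reported as a positive primary result, the 5% error rate no longer describes the trial's main claim. Section {17a} says the data analysts are not blinded, so with an unranked list the marker to emphasise could be chosen by people who know the allocation. The reader also cannot tell from the article whether there are five or six primary outcomes.

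**Working it through.** **Inputs from the protocol article.**
- Number of primary outcomes k: 5 (abstract) or 6 ({12}, culture counted once).
- Threshold per test: 0.05 ({20a}).
- hs-CRP means and SDs: 5.9 (2.57) and 3.6 (1.58); 30 per group; 10% dropout; a design effect whose value is not given ({14}).

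**Assumptions.** Tests are two-sided. There is one between-arm test per outcome. The markers share a common correlation, which the article does not give, so a range is shown. Each marker is signed so that positive means benefit (for IL-10, an increase).

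**1. The plan's own sample size.** Pooled SD = √((2.57² + 1.58²)/2) = 2.133, so d = 2.3/2.133 = 1.08 in absolute size. A two-sided t-test at 0.05 with 80% power needs 15 per arm, or 15/0.9 = 16.7, rounded up to 17, after dropout. The stated 30 is not reached without the design effect. With 30 × 0.9 = 27 completers per arm, the implied value is 27/15 = 1.8. This matters here only for step 4.

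**2. Independent markers, no true effect.**
- At least one P ≤ 0.05 in either direction: 1 − 0.95⁵ = 22.6%; 1 − 0.95⁶ = 26.5%.
- At least one in the favourable direction: 1 − 0.975⁵ = 11.9%; 1 − 0.975⁶ = 14.1%.

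**3. Correlated markers** (simulation, 500,000 draws of equicorrelated normal test statistics).

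| Correlation | Either direction, k = 5 | Either direction, k = 6 | Favourable, k = 5 | Favourable, k = 6 |
|---|---|---|---|---|
| 0 (exact) | 22.6% | 26.5% | 11.9% | 14.1% |
| 0.3 | 20.9% | 24.1% | 10.5% | 12.2% |
| 0.5 | 18.2% | 20.7% | 9.0% | 10.4% |
| 0.7 | 14.8% | 16.4% | 7.3% | 8.2% |
| 0.9 | 10.2% | 10.8% | 5.1% | 5.4% |

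The nominal figures are 5% in either direction and 2.5% in the favourable one. Even at correlation 0.9 both are about doubled.

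**4. What control would cost.** Holm tests the smallest P value at 0.05/k: 0.01 for five outcomes, 0.0083 for six. Using that threshold for all outcomes (Bonferroni) gives an error of 1 − 0.99⁵ = 4.9% if independent; Holm likewise holds it at or below 5%. Power for hs-CRP at d = 1.08 at this strictest step:

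| Completers per arm | α = 0.05 | α = 0.01 | α = 0.0083 |
|---|---|---|---|
| 27 (no design effect) | 97% | 90% | 88% |
| 15 (27/1.8, design effect real) | 81% | 58% | 55% |

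In the second case, 80% power at the stricter threshold would need 22 × 1.8/0.9 = 44 per arm for five outcomes, or 23 × 1.8/0.9 = 46 for six. The article gives no effect sizes for the other markers, so their power cannot be computed.

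**The case against.** **The success rule is assumed.** The error figures need any single positive marker to count as success. The article neither says nor excludes this, and a rule requiring all outcomes to be positive would not inflate the error. This stands: the figures are conditional. But the missing rule is itself part of the defect.

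**An analysis plan could supply the control.** Multiplicity procedures are often placed there, and the threshold sentence does not strictly forbid adjusted P values. This has some force. However, the article does not leave the matter open: it labels all these outcomes primary and sets one threshold for every analysis. Followed as written, it gives the inflated rate.

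**The size can be overstated.** A reader might infer a 20–26% chance of a false claim of anti-inflammatory benefit. The documents do not support that. Figures of that size count results in both directions, and about half would show a marker worsening. They would apply to benefit alone only if each test were one-sided at 0.05 and the markers nearly uncorrelated, and sidedness is not stated.

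**Control is not nearly free.** A reader might infer this from the 90% power for hs-CRP. It holds for that marker only, and falls to 58% if the implied design effect is real.

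**hs-CRP need not be the sole primary outcome.** Section {14} uses it because comparable trials were lacking, not because it matters most. Outcomes {12} deliberately spans blood, lung and gut. This stands, and so the choice is left to the sponsor.

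**The mismatches in the list are a lesser matter.** An abstract condenses, and Table 2 is a summary. The passages still disagree, but nothing shows that viral culture is the part in error.

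**Conclusion.** The point holds. Five or six co-equal primary outcomes, each judged at 0.05 with no success rule or adjustment, do not give a 5% error rate for the trial's main claim unless all are required to be positive. If any one marker suffices, the chance of at least one false-positive primary result in either direction is about 23–27% under independence and about 18–24% at correlation 0.3–0.5. The favourable half is about 9–14% over the same range, roughly four to six times the nominal 2.5% (9.0/2.5 = 3.6; 14.1/2.5 = 5.6). These figures assume two-sided tests, one test per outcome and no true effect on any marker. The correlations are assumptions. The existence of the defect does not depend on them, only its size.

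**What to change.** Before any analysis by treatment arm, amend {12} and {20a} to do one of the following:

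- **Keep all primary outcomes and apply Holm across them**, stating the number of outcomes and that tests are two-sided. This keeps the systemic, lung and gut scope.
- **Name one primary outcome at two-sided 0.05** and make the others secondary, or test them in a fixed, stated order that stops at the first non-significant result. hs-CRP is the marker already used for sizing, but the choice is the sponsor's.

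In either case, make the primary list agree between the abstract and {12}. Reconcile the bacterial and viral culture named in {12} with the bacterial-only methods in {18a} and Table 2, either by adding a viral method or by changing the outcome.

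Cost: wording in the protocol, analysis plan and registry, with no new visits or assays. Naming one primary outcome needs no change in sample size, but a lone positive on another marker no longer counts as primary success. Holm costs power: for hs-CRP at its strictest step with five outcomes, about 90% remains without a design effect and about 58% if the implied 1.8 is real. Power for the other markers is unknown. The sponsor should state the design effect before choosing.

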#### Participant timeline {13}

Nutritional recommendations will be provided to all the patients and/or their parents and legal guardians stand on the CF requirements and adjustable CREON dosing to the level of dietary fat. In addition, the patients and their parents completed the CFQ depend on age.

Anthropometric measurements (weight and height) will be performed using a digital scale (model: SECA). Body weight will be measured without shoes, and height will be measured in the standing position without shoes with the heels stuck to the wall and the head looking frontwards with the accuracy of 0.5 cm.

The fecal examination will be performed before and after the intervention. Before intervention, fecal sample will be evaluated for bacterial over growth and parasite specially giardia by checking stool PH and trophozoites or cysts of giardia. Any positive result will be treated with antibiotics before stating the trials.

Blood sampling will be performed before and after the intervention. Approximately 5 mL of blood will be collected, immediately centrifuged, with the serum separated from the sediment, and preserved at the minimum of temperature of − 20 °C.

The primary and secondary consequences of the treatment will be investigated before and 3 months after the treatment. The clinical evaluation and follow-up of medication use and side effects will also be carried out via phone call and paying monthly visit to the clinic, and the findings will privately be presented to the patients (Table 2).

**Table 2 Tab2:** Laboratory measurements, equipment, and normal range

Test	Test equipment	Company	Quality control	Normal range
**Hs-CRP**	Biochemical auto analyzer	Pars azmoon	Intra-assay CV: 2.2% Inter-assay CV: 1.1% Linearity (*R*^2^): 0.99 Detection limit: 0.1 mg/lit	Children: up 2.8 mg/L Adult: up to 5 mg/L
**IL-6**	ELISA kit	Demeditec	Intra assay CV: 4.2% Inter assay CV: 4.9% Accuracy: 99% Specificity: 94% Detection limit: 2 pg/ml	Up to 1.8 pg/ml
**IL-10**	ELISA kit	pars gene (Invitrogen)	Intra assay CV < 3% Inter assay CV < 8% Detection limit:2 pg/ml	1.2–7.8 pg/ml
**Calprotectin**	ELISA kit	EUROIMMUN	Intra assay CV: 3.4% Inter assay CV: 6.4% Linearity(*R*^2^): 0.99 Sensitivity: 94.1% Specificity: 95.5% Detection limit:1.9 μg/g	50–120 μg/g: borderline > 120 μg/g: positive
**Nasopharyngeal swab**	URT-S&C (gram-positive, gram negative, pseudomonas)	Variable		Culture: negative WBC count: up to 2–3

#### Sample size {14}

Due to the lack of clinical trials on the inflammatory effect of nano-curcumin in children with cystic fibrosis, we used HSCRP indices as an effect size. Therefore, the mean ± SD of hs-CRP indices in the curcumin and placebo groups were 5.9 ± 2.57 and 3.6 ± 1.58 respectively [27]. G- power analyzer was applied for calculating sample size between two independent populations with a confidence interval of 95% and power of 80%. By considering 10% dropout and using Deff (deign effect) for stratified sample, a total of 30 samples for each group was calculated. In total, 60 eligible patients with CF are needed to be included for the randomization aspect of this research.

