### Assignment of interventions: allocation

#### Sequence generation {16a}

The patients meeting the inclusion criteria will be enrolled in the study. Initially, stratified randomization will be used to divide the participants into two groups based on disease severity (severe/mild-to-moderate) using spirometry with 40% FEV1 cutoff range. Following that, random sampling will be applied to select the patients from each group to be administered with the nano-curcumin drop or nano-curcumin placebo drop using a random number table (Fig. 1).

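### The sample-size statement does not follow from its own inputs: they give 17 per group with dropout, and 30 rests on an unstated design effect that stratified randomisation does not justify; the planning means also run against the expected benefit without explanation

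*Protocol article*

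**What the plan says.** The section Sample size {14} of the protocol article bases the calculation on hs-CRP from a cited study: "the mean ± SD of hs-CRP indices in the curcumin and placebo groups were 5.9 ± 2.57 and 3.6 ± 1.58 respectively". It reports using G*Power for "calculating sample size between two independent populations", "with a confidence interval of 95% and power of 80" (per cent). It then allows for 10% dropout and adds a design effect: "using Deff (deign effect) for stratified sample, a total of 30 samples for each group was calculated". The total is 60. The design effect has no numerical value, and neither the units nor the nature of the indices is given.

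Trial design {8} describes a single-centre, parallel-group, placebo-controlled randomised trial. Under Sequence generation {16a}, "stratified randomization will be used to divide the participants into two groups based on disease severity", with a cutoff of 40% in FEV1, and patients are then allocated within each severity group. The Outcomes {12} section lists hs-CRP among the primary outcomes and frames these as changes from baseline to 3 months. The Background and rationale {6a} section expects curcumin to reduce inflammatory factors.

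**The concern.** Two things in one short section do not fit together.

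First, a standardised difference above 1 is large, and 80% power for it needs far fewer than 30 per group. The gap is filled by a design effect attributed to stratification. Design effects above 1 arise from clustering or unequal sampling weights, and this trial has neither.

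Second, the order of the planning means, as worded, gives curcumin the higher value of an inflammation marker that it is meant to lower.

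This section is the article's only justification for enrolling 60 children. As it stands, a reader cannot tell what difference the trial can detect, how much power it has, or which direction of effect was planned for. If the trial finds no difference in hs-CRP, a reader who relies on the stated 80% would give that result too little weight as evidence against the planned effect.

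**Working it through.** **Inputs** (Sample size {14}): means 5.9 and 3.6; SDs 2.57 and 1.58; 95% confidence, so α = 0.05; power 80%; two independent groups; 30 per group; dropout 10%. Sidedness is not stated, and I assume two-sided.

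**Effect size.**
- Difference = 5.9 − 3.6 = 2.3
- Pooled SD = √((2.57² + 1.58²)/2) = √((6.605 + 2.496)/2) = √4.551 = 2.133
- d = 2.3/2.133 = 1.078

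**Sample size without a design effect.**
- Normal approximation: n = 2(1.960 + 0.842)²/1.078² = 13.5, so 14 per group
- Exact noncentral t (the method G*Power uses): power is 78.4% at 14 per group and 81.3% at 15, so 15 per group
- With dropout: 15/0.9 = 16.7, so 17 per group and 34 in total

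The stated 30 is not reproduced.

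**Multiplier needed to reach 30.** Thirty per group less 10% leaves 30 × 0.9 = 27 completers. The implied design effect is 27/15 = 1.80, and 15 × 1.80/0.9 = 30 exactly.

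**Other readings at 80% power.**

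| Assumption | n per group | With 10% dropout | Implied multiplier (27/n) |
|---|---|---|---|
| Two-sided t, pooled SD 2.133 | 15 | 17 | 1.80 |
| One-sided t, pooled SD | 12 | 14 | 2.25 |
| Two-sided Mann-Whitney, worst-case efficiency 0.864, pooled SD | 17 | 19 | 1.59 |
| Two-sided t, SD 2.57 in both arms | 21 | 24 | 1.29 |
| Two-sided Mann-Whitney, worst-case efficiency, SD 2.57 | 24 | 27 | 1.13 |

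None of these reaches 30 without a multiplier.

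**Does stratification supply the multiplier?** Individuals are randomised at one centre within two severity strata, so there is no within-cluster correlation. If the analysis adjusts for severity, between-stratum variation leaves the error term, and the variance stays the same or falls, apart from one degree of freedom. If the analysis ignores severity, the overall SD used for planning already contains that variation. Neither case gives a design effect above 1.

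**What 30 per group delivers** (27 completers, two-sided α = 0.05, t-test):
- Power at d = 1.078: 97.3%
- Power at SD 2.57 (d = 2.3/2.57 = 0.895): 89.7%
- Difference detectable with 80% power: 0.777 SD, or 0.777 × 2.133 = 1.66 in the unstated units of the indices, against the 2.3 planned

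**Direction.** As worded, curcumin minus placebo is +2.3. Exchanging the labels changes the sign but leaves |d| and n unchanged, so this affects the meaning of the statement and not the sample size.

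**The case against.** The strongest reply is that the error is on the safe side. The trial enrols more than its stated inputs require, and neither design nor analysis changes. This stands, and it lowers the weight of the point. A reader might infer that the trial is too small or that 60 is wrong, but for hs-CRP at the stated effect the figures show the opposite.

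A second reply is that no slip of arithmetic is shown, since a multiplier of 1.80 gives exactly 30, and an article may leave the value to the full protocol. This stands in part. The documents do not show that 1.80 was the value used, and the implied figure falls to about 1.1 under the most cautious test and SD. But the complaint is not only that the value is missing. The reason given for the factor does not fit the design, and further detail on its size would not change that.

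A third reply concerns direction. It is tempting to read the means as showing that curcumin raises hs-CRP. The text does not go so far. The indices are undefined and without units, and the trial's outcomes are changes, so the figures could be reductions, in which case the order would be favourable. The labels could also be exchanged. The cited source is not at hand. What can be said is that the direction is reversed or unexplained.

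Finally, a reader might take the spare power as cover for a multiplicity correction. At α = 0.01 and 27 per group, power is 90% for hs-CRP at d = 1.078, but 73% at SD 2.57 and 57% at 0.777 SD. Outcomes {12} names at least six primary measures (IL-6, IL-10, hs-CRP, neutrophil count, culture, calprotectin), whereas 0.05/0.01 allows five, and no effect size is given for the others. That reassurance is not supported.

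**Conclusion.** The point holds as a defect of statement, of moderate weight. The stated inputs need 15 per group, or 17 with dropout. The step to 30 depends on an unstated factor of about 1.8 (about 1.3 at SD 2.57, about 1.1 with a worst-case Mann-Whitney loss added), and the reason offered for it does not apply to individual randomisation within strata. The 80% power claimed is not the power of 30 per group for the stated effect, which is about 97%, or about 90% at the larger SD. The direction of the planning means needs correction or explanation.

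These figures assume a two-sided 5% test, the t-test except where noted, 10% loss in each arm, and planning means and SDs that are correctly transcribed. They say nothing about power for the other primary measures.

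**What to change.** Change the text only and keep 60 patients.

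1. Check the cited source. State what the hs-CRP indices are (levels or changes) and their units, and correct or explain which arm each figure belongs to.
2. Delete the design effect.
3. Once the inputs are confirmed, state the sidedness and restate the calculation: 15 per group (17 with 10% dropout) gives 80% power for d = 1.08. If the source check changes the means or SDs, recompute first.
4. Give the real basis for enrolling 30 per group, whatever it was.
5. Report that 27 completers per group give about 97% power for that effect (about 90% at SD 2.57) and 80% power for a difference of 0.78 SD.

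The cost is a source check and one rewritten paragraph, with no effect on enrolment, design or analysis.
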